### Sample Size Calculation

We chose our CD4 depletion event rate based on the work of the CASCADE cohort which displays an average CD4 depletion of 114 (32-229) cells/μl per year and where 54% of individuals had a decline > 100 cells/μl per year if CD4 evaluations were rare, as in Rwanda [33]. We expect that the majority of participants in our study, about 60%, will enter the study with a CD4 at risk of reaching 350 cells/μl within the first year as most evidence demonstrates that patients in East Africa initiate treatment due to symptomatic HIV with a median CD4 of 141 to 169 (depending on source). Thus, patients with a high CD4 will be somewhat more rare to enroll [34,35].

We applied several sample sizes to display that even small changes in the relative risk of the intervention will yield a large impact on the required sample size (see Table 1). Our three sample size assumptions are based on the likelihood of an intervention delivering a small, moderate or large effect (relative risk reduction of 10, 25, and 50%). Given that we do not have strong evidence from previously completed trials, we are assuming the event of depleting CD4 status will occur in 60% of control patients at one year and 60% of experimental patients at one year if the intervention delivers no effect. Table 1 provides the estimates required for power of 80% and an alpha of 0.05.

**Table 1 T1:** Sample Size Calculation estimates

RRR	Control event rate	Experimental event rate	Sample size	Power
10%	60%	55%	2312	80%
25%	60%	44%	314	80%
50%	60%	29%	76	80%

We employed several methods to make these calculations. The below estimates are based on Markov Chain Monte Carlo Methods whereby we explored the impact of adherence/retention to the intervention and examined the differing possible risks of an underlying disease event. We performed 5,000 simulations for each estimate. As we employ informed estimates, using a Bayesian profile, our estimates may differ slightly compared with other software approaches. However, they should not differ to an important amount.

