Based on these calculations and our resources, we aim to enroll 300 patients in the trial. This leads to an RRR slightly lower than 25% and represents a very important reduction in events. Recognizing that no single trial can provide definitive evidence of effectiveness, this trial will contribute to the overall evidence of selenium supplementation for CD4 maintenance [36,37]. If control patients demonstrate lower rates of compliance to the intervention due to a lack of effects of, say, 20%, the power is increased to 96% and an alfa of 0.25. At the conclusion of our trial, we will conduct a meta-analysis to determine the overall power that current evidence contributes to answering this clinical question.

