### Analysis Plan

Analysis will be conducted jointly by the study team in Rwanda and in Canada using standard statistical software. The analysis and reporting of the results with follow the CONSORT guidelines [38]. The statistician/data analyst will be blinded to the study group. The process of patient selection and flow throughout the study will be summarized using a flow-diagram (See Figure 1). The analysis results of patient demographics and baseline outcome variables (both primary and secondary) will be summarized using descriptive summary measures: expressed as mean (standard deviation) or median (minimum-maximum) for continuous variables and number (percent) for categorical variables. We will adopt an intention-to-treat principle to analyze all outcomes, meaning that data from participants will be analyzed according to the group to which they were randomized even if they do not receive the allocated intervention. We will also use multiple-imputation to handle missing data. We will use the T-test for comparing groups on continuous outcomes and the chi-squared test for binary outcomes. We will consider a threshold of 0.05 as statistical significance. For all group comparisons, the results will be expressed as effect (risk ratio for binary outcomes), corresponding two-sided 95% confidence intervals and associated p-values. P-values will be reported to three decimal places with values less than 0.001 reported as < 0.001. Because the primary outcome is a composite outcome, we will assess heterogeneity between the included outcomes [39,40]. Further, adjusted analyses using the following baseline covariates (age, gender, nutritional status) will be performed using regression techniques to investigate the residual impact of key baseline characteristics on the outcomes. Goodness-of-fit will be assessed by examining the residuals for model assumptions and chi-squared test of goodness-of-fit. All analyses will be performed by a professional statistician.

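### Table 1's event rates do not match its relative risk reductions, and 300 patients give about 74% power for a true 25% reduction, with 80% reached only near 27%

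*Protocol article*

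**What the plan says.** In the protocol article, the Sample Size Calculation section considers a "small, moderate or large effect (relative risk reduction of 10, 25, and 50"%. For the control arm it states: "we are assuming the event of depleting CD4 status will occur in 60% of control patients at one year". On the design parameters it says: "Table 1 provides the estimates required for power of 80% and an alpha of 0.05".

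Table 1 pairs each RRR with a 60% control rate and these entries, all at 80% power:

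| RRR | Experimental rate | Sample size |
|---|---|---|
| 10% | 55% | 2312 |
| 25% | 44% | 314 |
| 50% | 29% | 76 |

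The figures are attributed to 5,000 simulations per estimate, which explored adherence and retention under informed, Bayesian inputs. The text expects no important difference from other software. It then sets enrolment at 300 and concludes: "This leads to an RRR slightly lower than 25% and represents a very important reduction in events".

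**The concern.** Three things in this section do not fit together. The experimental rates are not the control rate reduced by the stated RRRs. The sample sizes do not follow consistently from either the rates or the RRRs. The closing sentence says that enrolling fewer patients than the table requires lets the trial detect a smaller effect.

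The 25% row is the basis for enrolling 300, so its label, its rate and the sentence drawn from it need to agree. If they stay as printed, a reader of a null result could believe the trial had at least 80% power against a 25% reduction, when by the article's own type of calculation it had less.

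**Working it through.** **Inputs.** Control rate 60% at one year, 80% power and alpha 0.05 come from the Sample Size Calculation section. The Analysis Plan supplies the two-sided reading ("corresponding two-sided 95% confidence intervals and associated p-values") and the test ("We will use the T-test for comparing groups on continuous outcomes and the chi-squared test for binary outcomes"). The allocation ratio is not stated; I assume 1:1, so 150 per arm. No loss figure is given.

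**Step 1: rates against RRRs.** Experimental rate = 60% × (1 − RRR).

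| Stated RRR | Rate it implies | Rate printed | RRR of the printed rate |
|---|---|---|---|
| 10% | 54% | 55% | 1 − 55/60 = 8.3% |
| 25% | 45% | 44% | 1 − 44/60 = 26.7% |
| 50% | 30% | 29% | 1 − 29/60 = 51.7% |

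Rounding is not the cause, since 54, 45 and 30 are exact. Diluting the effect for non-adherence is not the cause either: it would move every experimental rate up towards 60%, yet 44% and 29% lie below the implied rates.

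**Step 2: the sample-size column.** With p̄ = (p1 + p2)/2, the patients needed per arm are

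- pooled: [1.960·√(2p̄(1−p̄)) + 0.842·√(p1(1−p1) + p2(1−p2))]² / (p1−p2)²
- unpooled: (1.960 + 0.842)²·[p1(1−p1) + p2(1−p2)] / (p1−p2)²

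Example for 60% v 45%, pooled: (1.384 + 0.588)² / 0.15² = 172.8, so 173 per arm and 346 in total.

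| Rates | Total N, pooled / unpooled | Table 1 |
|---|---|---|
| 60 v 55 (printed) | 3,068 / 3,062 | 2312 |
| 60 v 54 (10% RRR) | 2,136 / 2,130 | 2312 |
| 60 v 44 (printed) | 304 / 300 | 314 |
| 60 v 45 (25% RRR) | 346 / 342 | 314 |
| 60 v 29 (printed) | 80 / 74 | 76 |
| 60 v 30 (50% RRR) | 84 / 80 | 76 |

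The second and third rows roughly reproduce from the printed rates: an unrounded 44.26% returns 314, and 76 lies between 74 and 80. The first row does not. At its printed rates it is about 25% too small (2312/3068 = 0.75), and power at 2312 is 68%. Against a true 10% RRR it is about 8% larger than needed. One-sided, continuity-corrected and unpooled formulas were also tried; none reproduces all three rows.

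**Step 3: what 300 patients give.** Power = Φ{[|p1−p2| − 1.960·√(2p̄(1−p̄)/n)] / √([p1(1−p1) + p2(1−p2)]/n)} with n = 150.

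- 60% v 45%: (0.15 − 1.960 × 0.05766)/0.05701 = 0.649, so power is 74.2%. The unpooled formula gives 74.9%, the exact chi-squared calculation 75.9%, and the exact calculation with Yates correction 72.1%.
- 60% v 44%: power is 79.5%.
- Setting power to 80% and solving for the experimental rate gives 43.9%, an RRR of 1 − 43.9/60 = 26.8% (27.9% with continuity correction).

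**Step 4: losses, as an assumption only.** The same formula with fewer evaluable patients gives:

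| Assumed loss | Evaluable | Power, 60 v 45 | RRR at 80% power |
|---|---|---|---|
| 5% | 285 | 72.0% | 27.5% |
| 10% | 270 | 69.6% | 28.3% |
| 20% | 240 | 64.5% | 30.0% |

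**Step 5: direction.** This needs no formula. With power, alpha and control rate held fixed, if 314 patients are needed for a 25% RRR, then 300 can detect only a larger one.

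**The case against.** The strongest reply is that the error is small where it counts. At the rates printed for the target row, 60% v 44%, 300 patients give 79.5% power, and 314 slightly exceeds the 300 to 304 required. The 74% appears only when 44% is replaced by 45%. That is fair, and it means the 25% row is mislabelled rather than undersized at its own rates. It does not help the closing sentence, which speaks of a 25% RRR.

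Second, the figures come from simulations whose inputs this condensed article does not show, so the printed rates could be simulation averages. That could excuse small differences. It cannot reverse the direction of the conclusion or explain the first row, and the article itself expects no important difference from other software. No design decision rests on the first row, however.

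Third, the primary outcome is time to event over 24 months, so the one-year comparison of proportions may not describe the trial's real power. Under an added constant-hazard assumption, 60% v 45% at one year implies 84.0% v 69.75% at 24 months, with about 90% power by log-rank and about 84% by chi-squared. If the 25% is instead read as a hazard ratio of 0.75, log-rank power at 24 months is about 60%. So the 74% belongs to the one-year calculation and should be labelled so. But the article sizes the trial on one-year proportions, and a calculation it does not make cannot support the one it prints.

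Fourth, a one-sided 5% test would bring the detectable RRR at 300 down to 23.8%. The Analysis Plan is two-sided, and the one-sided formula gives 240 for the 44% row, not 314.

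Finally, reported confidence intervals will show what a null result excludes. They do, but that does not correct a wrong statement of the design's sensitivity.

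**Conclusion.** The concern holds. The printed rates correspond to RRRs of 8.3, 26.7 and 51.7%, not 10, 25 and 50%. The statement that 300 patients detect an RRR a little below 25% is wrong in direction whatever the formula. In size, 300 patients give about 74% power for a true 25% RRR (72 to 76% across the variants above), where 342 to 346 would be needed for 80%. The RRR detectable with 80% power is about 26.8%.

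The shortfall for the target effect is therefore moderate, about 6 percentage points of power. The largest numerical discrepancy is in the first row, about 750 patients at its printed rates. The power figures rest on 1:1 allocation, a two-sided 5% test, one-year proportions and no losses.

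**What to change.** 1. In Table 1, either change the experimental rates to 54, 45 and 30%, or keep the rates and relabel the RRRs as 8.3, 26.7 and 51.7%. Then recompute the sample-size column on the chosen basis. If the simulations are kept as the source, state the adherence, retention and risk inputs that produce each entry.
2. Replace the sentence on what 300 patients achieve with wording such as: For a two-sided 5% comparison of one-year event proportions with a 60% control rate and 1:1 allocation, 300 patients give about 74% power for a 25% RRR; 80% power is reached for an RRR of about 27%, before losses.
3. If the sponsor prefers to rest power on the 24-month time-to-event outcome, give that calculation with its hazard assumptions instead.

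The cost is restated figures that are slightly less favourable. Enrolment, endpoint and test need not change.

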### Randomization

Participants will be randomized using a simple randomized block design to receive either selenium or an identically appearing placebo to be taken once daily for 24 months. The Rwandan Ministry of Health recommends the use of co-trimoxazole, a sulfonamide antibiotic combination of trimethoprium and sulfamethoxazole used for the treatment of a variety of bacterial infections, for all HIV-infected patients. Therefore, all participants will also receive co-trimoxazole irrespective of experimental assignment. Participants who do not return to the clinic as scheduled will be followed up at home.

Study participants will be identified by a unique study identification number. The randomization schedule will be prepared by the product manufacturer, Seroyal, and the randomization sequence will be concealed from the study investigators and providers. Study participants will be assigned a specific allocation number. An unblinding list will be kept at the site of the manufacturer and will be provided as needed to the Data and Safety Monitoring Officer (DS). Site study personnel (investigator and clinical personnel monitoring the safety and laboratory assay results) and study participants will be blinded with respect to the allocation. Unblinding of an individual study participant will be indicated in the event of a medical emergency where the clinical management/medical treatment of the study participant could be altered by knowledge of the group assignment allocation of the investigational product.

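### The claim that 20% lower compliance among controls raises power to 96% at an alpha of 0.25 is unsupported and contradicts the trial's own alpha of 0.05

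*Protocol article*

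**What the plan says.** All places are in the protocol article.

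- **Sample Size Calculation, Table 1 and the text before it.** The design alpha and power are fixed: "Table 1 provides the estimates required for power of 80% and an alpha of 0.05". The control assumption is an event in "60% of control patients at one year". The row for a 25% relative risk reduction gives 60% versus 44%, a sample size of 314 and 80% power.
- **Sample Size Calculation, closing paragraph.** The target is set: "we aim to enroll 300 patients in the trial". The paragraph then supposes that controls comply less, by some 20%, because they notice no effect, and concludes that "the power is increased to 96% and an alfa of 0.25".
- **Analysis Plan.** "We will consider a threshold of 0.05 as statistical significance". Results are to carry "corresponding two-sided 95% confidence intervals and associated p-values". Outcomes are analysed by intention to treat.
- **Randomization.** "Participants will be randomized using a simple randomized block design to receive either selenium or an identically appearing placebo". Both arms also receive co-trimoxazole. The allocation ratio is not stated.

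**The concern.** The sentence raises two separate problems.

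First, alpha is chosen at the design stage and does not move with compliance. A value of 0.25 conflicts with the 0.05 stated in the same section and again in the Analysis Plan.

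Second, the mechanism does not work. A control patient who skips placebo capsules loses no active treatment, still receives co-trimoxazole, and is still counted as a control. The text gives no reason why the control event rate should rise, and without such a rise the contrast between the arms, and hence the power, stays where it was.

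At stake is what a reader takes the trial to be able to detect. This is the only compliance scenario that the section puts a number on. It suggests that poor compliance helps and that power may reach 96%, when at the trial's own alpha it is nearer 74% to 80%.

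**Working it through.** **Inputs.** Control rate p1 = 0.60 and experimental rate p2 = 0.44 (Table 1, 25% row). As a variant, p2 = 0.60 × 0.75 = 0.45, the exact 25% reduction. Total 300, taken as n = 150 per arm (1:1 is my assumption). Alpha 0.05, two-sided; two-sidedness is stated for the confidence intervals and assumed here for the power.

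**Formula** (two-proportion z test, pooled variance under the null):

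power = Φ[(p1 − p2 − z·s0)/s1], where s0 = √[2·p̄(1 − p̄)/n], s1 = √[(p1(1 − p1) + p2(1 − p2))/n] and p̄ = (p1 + p2)/2.

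**Step 1: reproduce Table 1.** With 314 patients (n = 157) and 60% versus 44%: s0 = 0.0564, s1 = 0.0557, z = 1.960. (0.16 − 1.960 × 0.0564)/0.0557 = 0.889, so power is 81.3%. Table 1 says 80%, so the method is close enough to the authors' simulation for this purpose.

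**Step 2: power at the planned size and alpha (n = 150).**
- 60% versus 44%: s0 = 0.0577, s1 = 0.0569; (0.16 − 1.960 × 0.0577)/0.0569 = 0.824; power 79.5%.
- 60% versus 45%: s0 = 0.0577, s1 = 0.0570; (0.15 − 1.960 × 0.0577)/0.0570 = 0.649; power 74.2%.

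**Step 3: apply the stated scenario.** If 20% of controls stop an inert placebo, their rate is 0.8 × 0.60 + 0.2 × 0.60 = 0.60. Nothing in step 2 changes. If the 20% meant controls lost from the analysis (120 versus 150, 60% versus 44%), power would fall to 74.6%.

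**Step 4: what would give 96%?**

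| Change | Rates | Power |
|---|---|---|
| Alpha 0.25 two-sided, 300 in total | 60% v 44% | 95.0% |
| Alpha 0.25 two-sided, 314 in total | 60% v 44% | 95.6% |
| Alpha 0.25 two-sided, 300 in total | 60% v 45% | 92.9% |
| Alpha 0.05, 300 per arm | 60% v 45% | 95.9% |
| Alpha 0.025 two-sided, 300 per arm | 60% v 44% | 95.6% |
| Alpha 0.05, 300 in total, higher control rate | 65% v 44% | 95.8% |

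Solving for exactly 96% at alpha 0.05 with 300 in total gives a control rate of about 65% (against 44%) or 66% (against 45%).

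**Step 5: a misprint for 0.025?** With 300 in total and 60% versus 44%, alpha 0.025 gives 70.5% two-sided or 79.5% one-sided, not 96%.

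**Step 6: non-compliance in the selenium arm.** Assume that Table 1's rates describe full adherence and that 20% of the selenium arm gets no effect.
- 0.8 × 0.44 + 0.2 × 0.60 = 0.472; power 60.5% at alpha 0.05.
- 0.8 × 0.45 + 0.2 × 0.60 = 0.48; power 55.0% at alpha 0.05.

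**The case against.** The best defence is that the sentence is a hypothetical aside. The enrolment target is set before it appears, and no test or decision rule uses 0.25. The main power statement roughly reproduces at the design alpha. All of that stands. A reader might infer that the trial will tolerate a 25% false-positive rate; the documents do not support this, because the Analysis Plan fixes 0.05 with two-sided 95% intervals.

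A reader might also infer that the whole rise to 96% comes from relaxing alpha to 0.25. Step 4 shows that this is plausible but not established. The match at the planned size is 95.0%, or 92.9% with an exact 25% reduction, and other routes land as close. Those routes need a sample or a control rate that the protocol does not state, but they mean that the numerical match does not identify the source.

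A third tempting reading is that selenium non-adherence definitely brings power down to 55% to 60%. The section says that its simulations looked at adherence and retention, without saying how. If Table 1 already allows for imperfect adherence, diluting it again counts the loss twice. For the same reason it would be unfair to say that the protocol ignores adherence, and the Intervention section plans monthly counselling.

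Finally, the authors' Bayesian simulation cannot be rerun. However, they say that it should agree with other software to within an unimportant amount, and a gap of about 16 points (96 − 79.5) or more is not unimportant.

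**Conclusion.** The sentence is wrong as written. Its alpha contradicts the design and analysis alpha, and its mechanism does not change the control event rate. At alpha 0.05 two-sided, 300 patients give about 80% power (60% versus 44%) or 74% (60% versus 45%), so the stated 96% is too high by roughly 16 to 22 points. This rests on 1:1 allocation, a two-sided test, an inert placebo and the protocol's 60% control rate. Reading 0.25 as 0.025 does not rescue it.

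Where the 96% came from cannot be determined from the document. The error is confined to a supporting statement: it does not set the sample size or the analysis. It does, however, state a power that the design does not have.

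**What to change.** Delete the sentence, or replace it with power at two-sided alpha 0.05 for 300 patients: about 80% for 60% versus 44%, or 74% for 60% versus 45%.

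A compliance scenario is optional. If one is kept, apply it to the selenium arm and state the assumption. For example: if Table 1's rates assume full adherence and 20% of the selenium arm gets no effect, the selenium event rate becomes 47.2% (from 44%) or 48% (from 45%), and power about 60% or 55%. If Table 1 already allows for non-adherence, say so and give no further dilution.

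The cost is one sentence and a less favourable figure. Enrolment, conduct and analysis are unaffected.

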### Analysis Plan

Analysis will be conducted jointly by the study team in Rwanda and in Canada using standard statistical software. The analysis and reporting of the results with follow the CONSORT guidelines [38]. The statistician/data analyst will be blinded to the study group. The process of patient selection and flow throughout the study will be summarized using a flow-diagram (See Figure 1). The analysis results of patient demographics and baseline outcome variables (both primary and secondary) will be summarized using descriptive summary measures: expressed as mean (standard deviation) or median (minimum-maximum) for continuous variables and number (percent) for categorical variables. We will adopt an intention-to-treat principle to analyze all outcomes, meaning that data from participants will be analyzed according to the group to which they were randomized even if they do not receive the allocated intervention. We will also use multiple-imputation to handle missing data. We will use the T-test for comparing groups on continuous outcomes and the chi-squared test for binary outcomes. We will consider a threshold of 0.05 as statistical significance. For all group comparisons, the results will be expressed as effect (risk ratio for binary outcomes), corresponding two-sided 95% confidence intervals and associated p-values. P-values will be reported to three decimal places with values less than 0.001 reported as < 0.001. Because the primary outcome is a composite outcome, we will assess heterogeneity between the included outcomes [39,40]. Further, adjusted analyses using the following baseline covariates (age, gender, nutritional status) will be performed using regression techniques to investigate the residual impact of key baseline characteristics on the outcomes. Goodness-of-fit will be assessed by examining the residuals for model assumptions and chi-squared test of goodness-of-fit. All analyses will be performed by a professional statistician.

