**Methods and Design:**

A 24-month, multi-centre, patient and provider-blinded, randomized, placebo-controlled clinical trial involving 300 pre-antiretroviral therapy (ART) HIV-infected patients will be carried out at two sites in Rwanda. Patients ≥ 21 years of age with documented HIV infection, CD4 cell count of 400-650 cells/mm^3^, and not yet on ART will be recruited. Patients will be randomized at each study site using a randomized block design to receive either the selenium micronutrient supplement or an identically appearing placebo taken once daily. The primary outcome is a composite of time from baseline to reduction of CD4 T lymphocyte count below 350 cells/mm^3^ (confirmed by two measures at least one week apart), or start of ART, or the emergence of a documented CDC-defined AIDS-defining illness. An intention-to-treat analysis will be conducted using stepwise regression and structural equation modeling.

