### Objectives and Hypothesis

The primary outcome of the study is time from baseline to reduction of CD4 T lymphocyte count below 350 cells/mm^3^ (confirmed by two measures at least one week apart), or start of ART, or the emergence of a documented CDC-defined AIDS-defining illness. We hypothesize that selenium supplementation in pre-ART patients will improve CD4 cell counts, decrease opportunistic infections, decrease HIV viral load, and delay ART initiation.

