### Outcomes

The primary outcome of the study is a composite outcome involving reduction of CD4 T lymphocyte count to below 350 cells/mm^3^ (confirmed by two measures at least one week apart), or start of ART, or the emergence of a documented CDC-defined AIDS-defining illness. Secondary outcomes includes viral suppression at 6, 12, 18, and 24 months; quality of life; weight gain; presence of opportunistic infections and mortality.

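### The primary outcome is defined as a time to event in two places and without time in a third, and the Analysis Plan names neither a survival method nor a time point for a binary comparison

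*Protocol article*

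**What the plan says.** The primary outcome is worded in two ways.

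- Abstract, Methods and Design: "The primary outcome is a composite of time from baseline to reduction of CD4 T lymphocyte count below 350 cells/mm^3", or ART start, or an AIDS-defining illness.
- Objectives and Hypothesis: "The primary outcome of the study is time from baseline to reduction of CD4 T lymphocyte count below 350", with the same two alternatives. The hypothesis includes delaying the start of ART.
- Outcomes: "The primary outcome of the study is a composite outcome involving reduction of CD4 T lymphocyte count to below 350 cells/mm^3", with the same alternatives but no mention of time.

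The Sample Size Calculation follows the wording without time. It uses event proportions at one year and relative risk reductions, while patients are followed for two years.

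Two accounts of the analysis are given.

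- Analysis Plan: "We will use the T-test for comparing groups on continuous outcomes and the chi-squared test for binary outcomes". For group comparisons, "the results will be expressed as effect (risk ratio for binary outcomes), corresponding two-sided 95% confidence intervals and associated p-values". Adjusted analyses for age, gender and nutritional status will use regression of an unnamed type. On incomplete data: "We will also use multiple-imputation to handle missing data".
- Abstract: "An intention-to-treat analysis will be conducted using stepwise regression and structural equation modeling".

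The text shown names no Kaplan-Meier estimate, log-rank test, Cox model, hazard ratio or censoring rule. The Analysis Plan gives no month at which a binary comparison would be made.

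**The concern.** A right-censored time to first event is neither a plain continuous nor a plain binary outcome, so neither named test suits the outcome as the abstract and the Objectives define it. Followed literally, the plan turns the composite into yes/no and discards when events happened. Yet the hypothesis concerns delay, and under the plan's own event rate most control patients would have had the event before follow-up ends.

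Two further gaps follow. With no time point fixed, the binary comparison could be made at 12 months (the sample size horizon) or at 24 months (the end of follow-up), and the two estimate different quantities. And because the abstract and the Analysis Plan describe different methods, the reader cannot tell which result will be the primary one. If stepwise selection were applied to the primary comparison, its nominal p-values and intervals would not be valid.

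**Working it through.** **Inputs.** From the Sample Size Calculation: control event rate 60% and experimental rate 44% at one year (Table 1, the 25% row), total 314, power 80%, alpha 0.05, planned enrolment 300. From Setting and Participants: two years of follow-up, with assessments at 6, 12, 18 and 24 months. Assumed: two-sided alpha, 1:1 allocation (150 per arm), constant hazards and no dropout unless stated.

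**1. The plan's own figure.** The usual two-proportion formula, with mean proportion 0.52, is

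n per arm = [1.96·√(2·0.52·0.48) + 0.8416·√(0.60·0.40 + 0.44·0.56)]² / 0.16² = (1.385 + 0.587)² / 0.0256 ≈ 152, or 304 in total.

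The plan prints 314. That is not an exact match, but 314 patients give 81.3% power by the same formula, and the plan attributes its figures to simulations whose inputs are not shown. The row behaves like a comparison of two proportions. Nothing below depends on the difference between 304 and 314.

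**2. Implied hazard ratio.** HR = ln(1 − 0.44) / ln(1 − 0.60) = (−0.580) / (−0.916) = 0.633.

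**3. Risks and risk ratio over time.**
- 12 months: 0.60 v 0.44; risk ratio 0.44/0.60 = 0.73.
- 24 months: 1 − 0.40² = 0.840 v 1 − 0.56² = 0.686; risk ratio 0.686/0.840 = 0.82.

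The hazard ratio is 0.633 throughout. The risk ratio depends on the month chosen.

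**4. Chi-squared power at 150 per arm.** Power = Φ{[d − 1.96·√(2p̄(1−p̄)/150)] / √([p₁(1−p₁) + p₂(1−p₂)]/150)}.
- 12 months: d = 0.16, p̄ = 0.52; Φ[(0.16 − 0.1131)/0.0569] = 79.5%.
- 24 months: d = 0.1536, p̄ = 0.7632; Φ[(0.1536 − 0.0962)/0.0483] = 88.3%.

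**5. Log-rank power (Schoenfeld).** Power = Φ(√D·|ln HR|/2 − 1.96), with |ln HR| = 0.458.
- 12 months: D = 150·(0.60 + 0.44) = 156; power 81.5%.
- 24 months: D = 150·(0.840 + 0.686) ≈ 229; power 93.3%.

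| Month | Risks | Risk ratio | Chi-squared | Log-rank |
|---|---|---|---|---|
| 12 | 60% v 44% | 0.73 | 79.5% | 81.5% |
| 24 | 84.0% v 68.6% | 0.82 | 88.3% | 93.3% |

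**6. Sensitivity.**
- If 20% of the information is lost by 24 months (assumed; the documents give no figure): 80.3% for chi-squared, 87.2% for log-rank.
- With 45%, which is exactly a 25% reduction from 60% although Table 1 prints 44%: HR 0.652; 24-month power 83.7% v 90.0%.
- Simulation with events seen only at six-monthly visits (60% v 44%, 150 per arm): about 81% for both tests at 12 months; about 88–89% v 93% at 24 months.

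**The case against.** The strongest reply is that the plan is coherent under one of its own definitions. The Outcomes section states the composite without time and the trial is sized on proportions, so a chi-squared test with a risk ratio fits that reading. This stands. It would go too far to say that no stated analysis fits the primary outcome; the conflict begins with how the outcome is defined. But even on that reading the comparison has no date.

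A second reply is that the regression planned for adjusted analyses could be a survival model, and that an article may leave such detail to the full protocol. It is fair that the plan does not offer only t-tests and chi-squared tests. But that regression is for covariate adjustment and its type is not given. Here the article does state its tests and effect measure, and they do not suit the outcome it defines twice, so this is more than omitted detail.

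A reader might also infer that the documents set out three rival primary analyses. They do not: the t-test and chi-squared test serve different types of variable, and the real discrepancy is between the abstract and the Analysis Plan. The Analysis Plan lists its adjustment covariates in advance, which limits the stepwise worry there. Structural equation modelling also appears in the abbreviation list and may belong to a fuller plan, so the documents call for reconciliation and do not show that it must be removed.

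Nor do the documents show that dropout will be mishandled. Patients who miss visits are to be followed up at home, and multiple imputation is legitimate under missing at random; ordinary censoring also rests on an untestable assumption. What is missing is a statement of how incomplete follow-up enters the primary comparison.

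**Conclusion.** The concern holds in this form. The primary outcome is a time to event in the abstract and the Objectives but carries no time in the Outcomes section. The named tests suit only the latter and have no time point, and the abstract's methods are not those of the Analysis Plan.

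It is tempting to infer that the trial would be underpowered. The figures do not support that. At 24 months the chi-squared test loses about 5 points to the log-rank test (88.3% v 93.3%) and stays above the planned 80%. At 12 months the gap is 2 points, and in the simulation with six-monthly visits there is practically none. These figures assume constant proportional hazards, equal arms and no dropout.

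The weight of the point lies elsewhere: delay, the stated hypothesis, is not estimated; the risk ratio has no single target, being 0.73 or 0.82 according to the month chosen; and the primary result could be selected after the data are seen. Because this determines the trial's main result, it should be settled before analysis.

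**What to change.** 1. Use the time-to-first-event definition in the abstract, the Objectives and the Outcomes section alike.
2. In the Analysis Plan, name one primary analysis over 24 months: a log-rank test stratified by site (the abstract says patients are randomized at each site), with a Cox hazard ratio and 95% confidence interval.
3. Censor event-free patients at their last assessment. State separately how deaths are handled; mortality is listed only as a secondary outcome, so a bare censoring rule would silently censor deaths.
4. Add an interval-censored sensitivity analysis, because scheduled CD4 counts are six months apart.
5. Keep the risk ratio as supportive, at one fixed time point stated in advance.
6. Align the abstract with the Analysis Plan: no stepwise selection for the primary comparison, and any structural equation modelling labelled exploratory.

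The cost is wording in four sections. No additional patients, visits or measurements are needed.
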